### Study design

The VF-HT-AF study is a randomized, multicenter, open-label, and four-arm parallel study to evaluate the effectiveness of valsartan, fluvastatin or a combination of both on recurrent AF in hypertensive patients with non-permanent AF in China. After providing informed consent, patients will be randomly assigned using a computer system to one of four groups (the valsartan group, the fluvastatin plus dihydropyridine CCBs group, the valsartan plus fluvastatin group, and the dihydropyridine CCBs group) by the School of Public Health of Tianjin Medical University, initially in a 1:1:1:1 ratio. Physicians, who should be qualified medical practitioners, screen and follow up the patients in hospital outpatient or inpatient clinics. All patients’ data will be collected using a standard case report form and transmitted to the central database at the data center. All centers will be regularly monitored for source data documentation. Missing or questionable data will be completed and corrected by queries.

If the candidate patients have not taken ARBs, ACEIs or statins in the past at least 14 days, they will be directly enrolled and randomized. If the candidate patients have taken ARBs, ACEIs or statins, they will be randomized after a 14-day washout period. Baseline data will be collected after the washout period.

The initial dose of fluvastatin will be 40 mg/day at night, while valsartan will be prescribed initially at 80 mg/day. The fluvastatin dose will be no less than 40 mg/day and that of valsartan will be no less than 80 mg/day during the follow-up period. Blood pressures in each group must reach the target blood pressure, which is set at <140/90 mm Hg.

### Follow-up

Clinical follow-up using standardized questionnaires will be performed every 3 months during the 2 years follow-up period from the assignment of each patient.

The dosages and types of all other anti-hypertensive, anti-hyperlipidemia, and anti-arrhythmic drugs used during the follow-up will be recorded for each patient. Ultrasound echocardiography will be performed before the patients enter the study and at the end of the follow-up period. 7-day Holter monitoring will be performed at the baseline, 6 month, 12 month and at the end of the follow-up period. Patients’ diaries, cardiac function (NYHA classification) and adverse events during the follow-up period will be collected every 3 months.

Throughout the study, patients should record diaries when they feel discomfort. Arrhythmia-related symptoms are self-evaluated or evaluated by 7-day Holter monitoring, which has five poles, is weighted 50 g, 2.0 × 2.7 cm, and can record ECG for 7 days. The 7-day Holter instruments were manufactured by BORSAM Co. in Shenzhen, Guangdong Province, China, and provided by the study’s sponsor, Tianjin Institute of Cardiology, Tianjin, China. The attending physicians will also record blood pressure and ECG during each follow-up. Unless necessary, anti-arrhythmic drug therapy will be discontinued during the study according to the attending physicians’ advice for each patient. The design of the study is shown in Fig. 1.

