### Primary outcome measures

The VF-HT-AF study will examine whether fluvastatin or valsartan has anti-arrhythmic effects on non-permanent AF, apart from their lipid-lowering and antihypertensive effects, in comparison with dihydropyridine CCBs. Also, it will confirm whether a combination of valsartan and fluvastatin has better effects on non-permanent AF than either drug alone.

Therefore, the primary outcome measure is the change in the development of paroxysmal AF into persistent or permanent AF, the development of persistent AF to permanent AF, as well as the change in incidence of overall and persistent AF recurrence, which will be evaluated by 7-day Holter monitoring and patients’ diaries during the 2-year’s follow-up of the four treatment groups.

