### Statistical analysis

All analyses will be performed based on the intention-to-treat principle with differences assumed to be significant at a two-sided *P* value < 0.05.

Baseline characteristics and follow-up information will be collected for each group through the questionnaire. Absolute values for each question will be used to calculate the mean value, standard deviation, median value, percentile, number of cases, and percentages per group. Statistical significance will be evaluated by analysis of variance or Kruskal–Wallis rank sum test for continuous variables and chi-squared test for categorical variables, respectively. Kaplan–Meier curves will be used to describe the time-dependent occurrence of events, and the log-rank test will be performed to compare survival distributions for the four groups. To adjust for possible baseline imbalances between groups, a Cox proportional hazards model will be used. A hazard ratio will be calculated. In addition, subgroup analyses will be performed corresponding to the nature of the data. All statistical analyses will be performed using SPSS statistical software (version 17.00, Chicago, IL, USA).

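### The planned log-rank test ignores AF on the baseline 7-day Holter, and the Cox model does not commit to using it; prespecify it for the AF recurrence analyses

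*Protocol article*

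**What the plan says.** **Recordings.** The Follow-up section of the protocol article states: "7-day Holter monitoring will be performed at the baseline, 6 month, 12 month and at the end of the follow-up period". One make of recorder is used, supplied by the sponsor. That gives one baseline recording and three after randomisation.

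**Outcome.** Under Primary outcome measures, the outcome combines progression of AF with "the change in incidence of overall and persistent AF recurrence". Both the recordings and the diaries kept by patients feed into it, so diary-detected events count as well as Holter findings.

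**Analysis.** In the Statistical analysis section, after Kaplan–Meier curves, "the log-rank test will be performed to compare survival distributions for the four groups". No stratification is mentioned. Then: "To adjust for possible baseline imbalances between groups, a Cox proportional hazards model will be used". No covariates are listed. The other tests named are "analysis of variance or Kruskal–Wallis rank sum test for continuous variables and chi-squared test for categorical variables".

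**Entry.** The entry criteria require AF in the year before enrolment and conversion to sinus rhythm. The article does not say what share of baseline recordings is expected to show AF.

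**The concern.** AF on a patient's own baseline recording is the baseline value of the outcome. It can differ between patients of the same AF class: one paroxysmal patient may show AF during those seven days and another may not. If it predicts recurrence, adjusting for it sharpens the treatment comparison even when the arms are perfectly balanced. The main reason to adjust for such a variable is precision, whereas the section gives chance imbalance as the purpose.

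The named log-rank test makes no use of the recording. The Cox model might, but nothing commits it to do so. What is at stake is power for overall and persistent AF recurrence, from data the trial already schedules for every patient. Validity is not at stake: the unadjusted log-rank test keeps its type I error.

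**Working it through.** **1. The plan's own figure.** The article gives 80% power, a two-sided 5% level, a 6.8% lower incidence of persistent AF, and 1404 patients, which is 1404/4 = 351 per arm. No control rate is given, so 1404 cannot be derived from the printed inputs. Reading 6.8% as percentage points and solving

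n = [1.960·√(2p̄(1−p̄)) + 0.842·√(p₁(1−p₁) + p₂(1−p₂))]² / 0.068²

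for n = 351 gives p₁ ≈ 15.2% and p₂ ≈ 8.4%. A control risk of about 15% is thus the value that best fits the stated size. It is inferred, not stated.

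**2. Model for the gain.** Two arms of 351 and time to first event over follow-up scaled to 1. A share q of patients has AF on the baseline Holter, and their hazard is HR_b times that of the others. The base hazard λ solves

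control risk = (1−q)(1−e^(−λ)) + q(1−e^(−λ·HR_b)).

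Example: risk 50%, q = 0.3, HR_b = 3 gives λ = 0.487, since 0.7 × 0.385 + 0.3 × 0.768 = 0.50. Treatment multiplies the hazard by HR_t within each baseline group. There were 3,000 simulated trials per row. Control risks, q, HR_b and HR_t are all assumptions.

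| Control risk (HR_t) | q, HR_b | Unadjusted log-rank | Stratified by baseline Holter AF | Gain (points) |
|---|---|---|---|---|
| 15.3% (0.55) | 20%, 2 | 75.9% | 76.4% | 0.5 |
| 15.3% (0.55) | 30%, 3 | 75.6% | 76.7% | 1.1 |
| 15.3% (0.55) | 40%, 5 | 73.7% | 77.3% | 3.6 |
| 50% (0.74) | 20%, 2 | 74.8% | 77.5% | 2.7 |
| 50% (0.74) | 30%, 3 | 68.9% | 75.4% | 6.5 |
| 50% (0.74) | 40%, 5 | 59.8% | 76.3% | 16.5 |
| 70% (0.78) | 20%, 2 | 72.9% | 75.9% | 3.0 |
| 70% (0.78) | 30%, 3 | 65.1% | 76.4% | 11.3 |
| 70% (0.78) | 40%, 5 | 52.1% | 78.0% | 25.9 |

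The Monte Carlo error of each power is about √(0.75 × 0.25/3000) = 0.8 points. Repeating the runs with another seed moved no power by more than about 2 points.

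When events are common, high-risk patients have their events early, the risk sets change composition, and the unadjusted hazard ratio drifts towards 1. Stratifying prevents this. When events are rare there is little depletion and little to gain.

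**3. A second model.** Here AF on each scheduled recording follows a random-intercept logistic model, again with 351 per arm and assumed inputs.

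- With AF on 22 to 36% of baseline recordings, stratifying the log-rank on first positive Holter raised power from 59.5 to 64.0%, 66.2 to 71.4%, 72.1 to 82.8% and 79.7 to 88.0%: gains of 4.5 to 10.7 points.
- With AF on only 4 to 12% of baseline recordings, stratifying gained about 1 to 5 points.
- With a cumulative control risk of 8 to 12%, it gained 0 to 3 points.
- Averaging the three follow-up Holters with baseline adjustment gave 72.1, 79.7, 88.9 and 92.8% in the same four scenarios as the first item: 12.6 to 16.8 points above the unadjusted log-rank.
- With no treatment effect, rejection was 4.3 to 5.6% for all three methods.

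This model counts scheduled Holters only, so its powers are not the trial's power for an outcome that also includes diary events.

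**The case against.** The strongest reply is that a baseline-adjusted Cox model with a hazard ratio is already planned, that its covariate list belongs in the SAP, and that first-event log-rank plus adjusted Cox is conventional and valid. Much of this stands. A reader might infer that the plan uses neither the baseline nor the later recordings. The article does not support that: the Cox covariates are unnamed and could include the baseline Holter, and the later Holters supply outcome events. What remains is what the text does fix, an unadjusted log-rank test and an adjustment justified by imbalance.

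A reader might also take the word change in the outcome as a within-patient change from baseline that no named test estimates. That reading is not needed. Incidence of recurrence is a group quantity, the outcome is tied to follow-up of the four groups, and the objective is stated as a comparison with CCBs. A between-arm difference is the natural meaning, and the named tests address it.

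The size of the gain is fairly challenged too. The sinus-rhythm entry rule may leave few positive baseline recordings, although paroxysmal AF is by definition recurrent. The event behind the sample size appears uncommon. Progression to permanent AF gains little from recordings made after it occurs.

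Finally, a model of scheduled Holters alone would drop diary-detected events, and recordings after a first recurrence may reflect anti-arrhythmic drugs or ablation. It should not replace the primary analysis.

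**Conclusion.** The point holds in a limited form: the Statistical analysis section does not commit to using the baseline value of the AF outcome for precision, though the recording is scheduled for every patient. Prespecifying it is better than the stated method.

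The gain is about 0 to 5 points of power for an uncommon event (risk of about 15% or less) or few positive baseline recordings. It is about 3 to 26 points when recurrence is common (about 40 to 70%) and baseline Holter AF is prognostic, with the upper end needing 40% positive and a fivefold hazard. The documents give neither the share with baseline AF, nor its prognostic strength, nor the recurrence risk, so no single figure can be claimed. For the persistent-AF event that best fits the sample size, the low range applies. A large, certain loss of power is not shown.

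**What to change.** In the Statistical analysis section, for overall and persistent AF recurrence:

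1. Name AF on the baseline 7-day Holter (yes/no), from the recording made before study treatment starts, as a stratum in the log-rank test and a covariate in the Cox model. Apply it to every between-arm comparison, whether or not the arms look imbalanced, and reword the purpose of the adjustment to include precision.
2. Optionally, add a supportive repeated-measures logistic model (GEE or mixed) of the committee-read Holter result at 6, 12 and 24 months, with arm, visit and baseline Holter AF. Keep the primary outcome and its diary-detected events unchanged.

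The cost of the first change is analysis text only, with no new visits, recordings or patients. The hazard ratio then refers to patients with the same baseline Holter status. The second change adds an odds ratio for AF on a recording, to be read alongside the first-event hazard ratio. The article reports that recruitment was under way, so both could be fixed before the data are analysed.

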**Fig. 1 Fig1:**
[figure not shown]
Flow-process diagram. BP, blood pressure; ECG, electrocardiography

### Compliance strategy

To maximize subjects’ compliance, first, we will have a thorough consent process for all participants. We will explain the schedule, potential side effects of treatment, and the responsibilities of the subjects in detail. Second, we will try to prevent dropouts by providing ongoing support to patients. A direct telephone line set up for this trial will enable the study team to communicate with the patients personally. An information sheet will be given to each participant providing them or their caregivers with means of urgent contact. Extra visits and free medical care will be arranged for any participant who feels harmed by the trial protocol. Certainly those participants in the control group should not experience any difference in their condition.

### Primary outcome measures

The VF-HT-AF study will examine whether fluvastatin or valsartan has anti-arrhythmic effects on non-permanent AF, apart from their lipid-lowering and antihypertensive effects, in comparison with dihydropyridine CCBs. Also, it will confirm whether a combination of valsartan and fluvastatin has better effects on non-permanent AF than either drug alone.

Therefore, the primary outcome measure is the change in the development of paroxysmal AF into persistent or permanent AF, the development of persistent AF to permanent AF, as well as the change in incidence of overall and persistent AF recurrence, which will be evaluated by 7-day Holter monitoring and patients’ diaries during the 2-year’s follow-up of the four treatment groups.

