## Methods/design

The VF-HT-AF study is designed as a prospective, randomized, open-label, four-arm parallel, and multicenter study. The objective of the study is to test the hypothesis that upstream therapy using valsartan or fluvastatin is more effective in reducing the recurrence of AF and the progress from non-permanent AF to permanent AF in hypertensive patients with non-permanent AF, compared with conventional antihypertensive therapy using dihydropyridine calcium channel blockers (CCBs). This study will be conducted according to the principles outlined in the Declaration of Helsinki. Written informed consent will be obtained from all patients prior to the study. The study protocol has been approved by the ethics committee of the Second Hospital of Tianjin Medical University (Clinical ethical review, 2012, No. 27) as well as other participating medical centers, which are secondary or tertiary healthcare providers in China, and should provide proof of laboratory quality control. The ethical bodies that approved our study in the various centers are listed in Additional file 1. If there is any amendment to the protocol, approval must again be sought from the ethics committee. The study is registered with the Chinese Clinical Trial Registry (ChiCTR-TRC-12002642). The protocol design is based on the Consolidated Standards of Reporting Trials (CONSORT) and Standard Protocol Items: Recommendations for Interventional Trials (SPIRIT, see Additional file 2), and study results will be reported according to these guidelines.

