### Expected implications

The VF-HT-AF study will determine the anti-arrhythmic effects of the ARB and statin on the recurrence of non-permanent AF associated with hypertension. It will also examine the mortality, morbidity, and perpetuation of the arrhythmia under valsartan, fluvastatin, dihydropiridine CCBs or combined treatment.

In particular, prevention of persistent and permanent AF would be expected to reduce hospitalization for heart failure, the incidence of stroke, morbidity, and mortality in patients with hypertension. This study will provide data to health care policymakers and the authors of clinical guidelines regarding the appropriate use of upstream therapy in hypertensive patients with AF and provide directions for future research.

Therefore, the results of this study will emphasize the role of upstream therapies in the prevention of AF in a Chinese hypertensive population and assist in the design of an optimal therapy for such patients.

However, one important limitation that might be present in this study is that it is an open-label trial, because we do not have enough funds to make the drugs in blinded versions. The drugs that the patients will use in our study are all provided in hospitals or pharmacies. The patients and doctors will know the drugs used. Another limitation is that the control group is not blank, so we do not test the fluvastatin effect alone. Because the patients in our study are hypertensive patients, they must, for ethical reasons, be treated with antihypertensive therapy. We chose the group receiving dihydropyridine CCBs as the control group, comparing them with the dihydropyridine CCBs plus fluvastatin group. If the recurrence of AF in the dihydropyridine CCBs plus fluvastatin group is less than the dihydropyridine CCBs group, it will be proved that fluvastatin can reduce the probability of non-permanent AF in patients with hypertension. There may be some combined effects of dihydropyridine CCBs plus fluvastatin, but we have to use antihypertensive drugs.

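### The objective of showing the combination better than fluvastatin alone does not match the randomized arms; the available contrast is valsartan in place of a CCB on a fluvastatin background

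*Protocol article*

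**What the plan says.** Under Primary outcome measures, the Protocol article asks "whether fluvastatin or valsartan has anti-arrhythmic effects on non-permanent AF", with dihydropyridine CCBs as the comparator. It then adds that "it will confirm whether a combination of valsartan and fluvastatin has better effects on non-permanent AF than either drug alone". Two other places also name fluvastatin without a CCB. The hypothesis in the opening paragraph of Methods/design is that "upstream therapy using valsartan or fluvastatin is more effective in reducing the recurrence of AF" than CCB-based therapy, and the first sentence of Study design gives the purpose as "to evaluate the effectiveness of valsartan, fluvastatin or a combination of both on recurrent AF".

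The only list of randomized arms, under Study design, reads "the valsartan group, the fluvastatin plus dihydropyridine CCBs group, the valsartan plus fluvastatin group, and the dihydropyridine CCBs group", allocated "initially in a 1:1:1:1 ratio". Fluvastatin without valsartan is therefore always given with a CCB.

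The section Expected implications agrees with that list. It states as a limitation that "the control group is not blank, so we do not test the fluvastatin effect alone", and explains that because the patients are hypertensive "they must, for ethical reasons, be treated with antihypertensive therapy". It names CCB plus fluvastatin versus CCB as the fluvastatin comparison and admits that the two drugs may have combined effects.

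**The concern.** Read literally, the objective promises two comparisons: the combination against valsartan alone and against fluvastatin alone. The arms supply the first. For the second, the nearest contrast is combination versus fluvastatin plus CCB, which changes two things at once: valsartan comes in and the CCB goes out.

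What is at stake is how a result is labelled. A difference between those two arms could be reported as a gain from combining the drugs, although it could arise because the CCB is worse than neutral for AF while valsartan adds nothing. Conversely, if the CCB is itself protective, a real gain from adding valsartan would be understated or hidden. The data cannot tell these cases apart. The article says its results are meant for policymakers and guideline authors, so the label matters. An analysis plan cannot repair this, because no analysis can supply a comparison for which no arm exists.

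**Working it through.** No figure in the plan is in dispute. The check is which contrasts the arms identify.

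**Step 1. Layout.** Write V for valsartan, F for fluvastatin and C for the CCB. The four arms form a 2×2 table:

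| | No fluvastatin | Fluvastatin |
|---|---|---|
| CCB | C | F+C |
| Valsartan | V | V+F |

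There is no row without an antihypertensive.

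**Step 2. Contrasts.** Let v, c and f be the log hazard ratios of valsartan, CCB and fluvastatin, each against not having that drug. Effects are taken as additive on the log scale, for illustration.

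- F+C versus C: (f + c) − c = f. Fluvastatin on a CCB background.
- V+F versus V: (v + f) − v = f. Fluvastatin added to valsartan.
- V versus C: v − c. Valsartan in place of a CCB.
- V+F versus F+C: (v + f) − (f + c) = v − c. Valsartan in place of a CCB, given fluvastatin.
- V+F versus F with no antihypertensive: v. Not identified by any pair of arms.

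The fourth contrast equals the fifth only if c = 0. Without interaction it equals V versus C, which is already the trial's main valsartan question.

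**Step 3. Can c = 0 be assumed from the document?** No arm goes without an antihypertensive, so the trial cannot test it. The Discussion section on valsartan cites an earlier hypertension trial with an unadjusted hazard ratio of 0.683 for persistent AF, valsartan against amlodipine. That is again a v − c quantity and does not show which drug drives the difference. The document gives no CCB-versus-nothing effect on AF.

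**Step 4. Size of the gap (illustration).** Suppose the true hazard ratio of V+F against fluvastatin alone is 0.80. The ratio of V+F against F+C is then 0.80 ÷ (hazard ratio of CCB against none):

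| CCB hazard ratio (assumed) | V+F versus F+C |
|---|---|
| 0.8 | 1.00 |
| 0.9 | 0.89 |
| 1.0 | 0.80 |
| 1.1 | 0.73 |
| 1.25 | 0.64 |

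**Step 5. Chance of a misattributed result (illustration).** Suppose valsartan adds nothing (v = 0) and the CCB multiplies the hazard by h. Take n = 1404 ÷ 4 = 351 per arm, from the number to be included under Sample size calculation. Let p be the two-year event proportion in F+C, assumed 0.30. Then:

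- p₂ = 1 − (1 − p)^(1/h)
- expected events D = n(p + p₂)
- z = ln(h)·√D ÷ 2
- probability = 1 − Φ(1.96 − z)

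| h | p₂ | D | z | Probability of a significant result favouring V+F |
|---|---|---|---|---|
| 1.1 | 0.277 | 202 | 0.68 | 10 % |
| 1.2 | 0.257 | 196 | 1.28 | 25 % |
| 1.3 | 0.240 | 190 | 1.81 | 44 % |

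With p = 0.11 the probabilities are 6, 12 and 19 %; with p = 0.50 they are 14, 38 and 65 %. All values of h and p are assumptions.

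**The case against.** The strongest reply is that the document already knows this. Expected implications discloses the limitation, justifies it, names the fluvastatin comparison to be used and admits possible combined effects. This stands, and it means the matter is one of reconciling sections. But the comparison named there is F+C versus C. It does not say how the combination is to be compared with fluvastatin, so the objective remains at odds with it.

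A second reply is that, where every patient needs an antihypertensive, the word alone can mean without the other study drug. On that reading both V+F versus V and V+F versus F+C exist, and the objective can be addressed. This is a fair reading, and a flat statement that the comparison cannot be obtained would go too far. It does not make the second contrast an add-on contrast, however. One sentence still presents an addition and a substitution as the same kind of gain.

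A reader might infer that the protocol defines the fluvastatin arm in two conflicting ways. It does not: the single arm list says fluvastatin plus CCB, Expected implications agrees, and the shorter descriptions name the drugs under study rather than an arm. Nor does the text promise that the combination will win; it says it will confirm whether it does.

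A reader might also take the 10, 25 and 44 % in the working as an inflated type I error. They are not. In that scenario the two arms truly differ, so the test is valid for the contrast it makes and only the label would be wrong. The calculation also assumes no CCB in the combination arm. The Follow-up section records other antihypertensive drugs, and no passage bars a CCB there; such use would shrink the gap.

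**Conclusion.** The point holds as a mismatch between one stated objective and the randomized arms. Combination versus valsartan answers whether adding fluvastatin helps. Combination versus fluvastatin plus CCB answers whether valsartan is better than a CCB in patients taking fluvastatin. The second supports a claim about adding valsartan to fluvastatin only under CCB neutrality for AF, which the trial cannot examine.

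This conclusion follows from the arm list and the article's own stated limitation, and needs no numerical assumption. The hazard ratios and probabilities in the working only show that the distinction could matter; they rest on assumed CCB effects and event rates. The allocation, sample size, endpoints and F+C versus C comparison are unaffected.

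**What to change.** Under Primary outcome measures, replace the comparison with either drug alone by the two contrasts the arms provide:

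- valsartan plus fluvastatin versus valsartan, which estimates the effect of adding fluvastatin;
- valsartan plus fluvastatin versus fluvastatin plus dihydropyridine CCB, which estimates valsartan in place of a CCB, given fluvastatin.

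State there that superiority of the combination over fluvastatin alone will not be claimed. Reconcile the short treatment descriptions in the opening of Methods/design and the first sentence of Study design with the arm list and with the limitation in Expected implications, naming the fluvastatin arm in full wherever a comparison is described.

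The cost is wording only: no arm, regimen or sample size changes. The downside is that one stated claim becomes narrower.
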